### Statistical analysis

Descriptive statistics will be used to present the outcomes of the study parameters and the socio-demographic data. Means and standard deviations will be calculated for variables on an interval scale and medians and interquartile ranges for ordinal variables. Proportions will be calculated for nominal variables.

Subgroup analyses will be performed for patients presenting in UWS versus MCS at baseline and for traumatic versus non-traumatic disorders of consciousness.

The proportions of patients transitioning from UWS to MCS and emergence from MCS to the conscious state will be calculated during and after EIN.

The course of recovery of consciousness (yes/no) over time will be analysed using Generalized Estimating Equations (GEE) analysis for logistic outcomes on an intention-to-treat basis. Assuming that data are missing at random, data imputation is unnecessary in GEE analysis; all observations are taken into account in contrast to complete case analyses. Recovery (yes/no) at each time point will be included as the dependent variable in the GEE model. Separate models will be generated for transitions from UWS to MCS and from MCS to the fully conscious state based on the CRS-R. Independent variables that will be added one by one to the models, include- measurement time (weeks), traumatic vs. non-traumatic aetiology, age at injury, and complications (yes/no or number). Significant predictors (*p* < 0.05) will be included in a multivariable model using a Bonferonni correction, dividing the significance level (alpha< 0.05) by the number of predictors included in the model.

Also using GEE analysis, the course of quality of life (EQ-5D-5L and Qolibri) and participation (CIQ) over time will be analysed using separate linear outcome models. The effects of time, cognitive (MoCa), behavioural (NPI), emotional (HADS), and motor status (FIM), and level of disability (DRS) and discomfort (NCS) on quality of life or participation during follow-up will be studied by adding these time-dependent variables (one by one) as independent variables to the models. Significant predictors (*p* < 0.05) will be added into a multivariable GEE-model to study the independence of these potential predictors on the outcomes using the Bonferroni correction.

In caregivers, self-efficacy (GSES) and caregiver strain (CSI) are measured, which will also be modelled using GEE analyses. Independent variables added to these models include age and gender of the caregiver and the level of consciousness (UWS, MCS, or conscious), and the cognitive (MoCA) and motor (FIM) status of the patients.

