**Fig. 1 Fig1:**
[figure not shown]
Study design

The EIN programme is standard care and is provided in a single specialised rehabilitation centre in the Netherlands. All hospitals in the Netherlands may refer patients who are eligible for EIN to this centre. Informed consent is obtained from the legal representative of each patient before the start of the study. Patients who show sufficient recovery of consciousness during the study trajectory will personally be asked consent for further participation in the study.

This study is not subject to the “Medical Research Involving Human Subjects Act”, determined by the Medical Ethics Committee of Erasmus MC, University Medical Centre Rotterdam (MEC-2019-0127).

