### EIN programme

The EIN programme is a subacute medical rehabilitation programme of 14 weeks (or less when recovery of consciousness occurs earlier) and meets the guideline recommendations for patients with PDOC published by the American Academy of Neurology [26]. An interdisciplinary rehabilitation team of a rehabilitation physician, a physician assistant, a neuropsychologist, cognitive rehabilitation therapists, physiotherapists, occupational therapists, speech therapists, nursing staff, dietician, and social worker uses an integrated approach in a 24/7 setting [19] with a minimum duration of 120 min therapy per day in which daily routines are built in together with a structured scheme of therapy and rest. The program is focused on optimizing the metabolic state, nourishment, respiration and skin condition, as well as diminishing the risk of infections and quick removal of invasive devices, like a tracheostomy tube or a urinary catheter, and recovery of the normal circadian cycle. Pharmacological treatments and structured stimulation of all sensory modalities (vision, hearing, smell, taste, touch, posture and motion, pain and temperature) aim to generate maximal arousal. As soon as the patient shows any voluntary reactions, reflecting a change from UWS into MCS, the focus of treatment changes from stimulation to training of cognitive functions. Motor rehabilitation aimed at optimising postural and motor activity helps restore bodily integrity and reduces the risk of complications (e.g., infection, thrombo-embolic complications, skin breakdown). For patients who reach MCS, increased time is spent on training mobility and self-care. Coping and self-efficacy of caregivers are addressed with psychoeducation, counselling and hands-on training in handling the patient.

After EIN, patients are discharged to 1) a regular neurorehabilitation setting in case of full recovery of consciousness and the ability to participate in a rehabilitation programme as judged by the rehabilitation physician, 2) to skilled nursing facilities, 3) sheltered housing or 4) possibly home (Fig. 2). Some skilled nursing facilities offer a prolonged intensive neurorehabilitation programme (PIN) for further recovery of consciousness during a period of up to 24 months post-injury. EIN is part of an academic network of expertise (EENnaComa) in which various healthcare institutes specialised in post-acute and long-term care of PDOC patients and their families are united.

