### Data collection

In 4 years we aim to include 72 patients. Structured data collection (Fig. 3) will take place at the start of the EIN programme at week 5, 10, and at EIN discharge (week 14). LOC assessment and registration of complications will be done weekly.

After discharge from EIN, follow-up measurements are planned at 28, 40, 52, and 104 weeks post-inclusion. These will take place at the patients’ actual health-care institution or residence.

All measurements conducted during the EIN programme are performed by trained members of the rehabilitation team. Follow-up measurements are performed by a trained research assistant.

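### The plan drops imputation under missing at random by appeal to a property that ordinary GEE does not have in general, so the recovery and other longitudinal estimates can be biased

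*Protocol article*

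**What the plan says.** The course of recovery (yes/no at each time point) is to be analysed "using Generalized Estimating Equations (GEE) analysis for logistic outcomes on an intention-to-treat basis". The missing-data rule follows directly: "Assuming that data are missing at random, data imputation is unnecessary in GEE analysis". The reason given is that "all observations are taken into account in contrast to complete case analyses". The article names no weights, no working correlation and no sensitivity analysis.

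Quality of life and participation "over time will be analysed using separate linear outcome models", also by GEE, and the caregiver outcomes are modelled by GEE as well. The missing-data sentence stands in the recovery paragraph only, but no other method for missing data is given for these models.

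On how data may be lost, the text after Fig. 1 (Study design and setting) states: "Patients who show sufficient recovery of consciousness during the study trajectory will personally be asked consent for further participation in the study". The EIN programme section sets a length of 14 weeks, "or less when recovery of consciousness occurs earlier". The Mortality section lists categories of death to be recorded.

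**The concern.** The sentence is a stated rule, not a gap that a fuller document might fill, and an analysis plan that follows it inherits the error. GEE solves moment equations. With incomplete follow-up, those equations keep mean zero if the chance of being observed is constant or depends only on covariates in the model. If that chance depends on earlier outcomes, they need not. Estimation under missing at random without imputation or weights is a property of correctly specified likelihood-based models. Using all available records improves on complete-case analysis, but it does not correct for selective loss.

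Re-consent fits this description closely. The recovery that triggers the request is observed, so refusal depends on an observed outcome: missing at random can hold while ordinary GEE is still not protected.

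GEE is the only inferential model in the article. The Discussion says the results will be used to benchmark the programme and to improve outcome prediction. An error of several points in the proportion recovered would carry into both uses.

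**Working it through.** **Inputs.** From the documents: binary recovery analysed by logistic GEE; visits at start, weeks 5, 10, 14 (discharge), 28, 40, 52 and 104; and "In 4 years we aim to include 72 patients". There is no stated figure to reproduce, because the article gives no dropout rate, recovery rate or working correlation. All of these are **assumed** below.

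**Step 1: why selective loss matters.** With independence working correlation and visit as a factor, the fitted recovery at a visit is the proportion recovered among those still observed. Let r be true recovery, and q1 and q0 the probabilities of being observed for recovered and non-recovered patients:

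estimate = r·q1 / [r·q1 + (1 − r)·q0].

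This equals r only if q1 = q0. Over seven post-baseline visits, 10% dropout per visit until recovery leaves a never-recovered patient observed at week 104 with probability 0.90^7 = 0.478. If dropout stops at recovery, q1 is larger and the estimate is too high. If recovered patients leave more often, it is too low.

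**Step 2: absorbing recovery.** 5,000 patients; frailty SD 1.5 on the logit hazard; dropout depends only on the last observed state. Week 104, independence:

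| Dropout per visit, not recovered / recovered | True | GEE | Bias (points) |
|---|---|---|---|
| 10% / 0% | 51% | 62% | +11 |
| 5% / 15% | 53% | 43% | −10 |
| equal | – | – | none |

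The second row has the direction that re-consent would produce. With exchangeable correlation and a separate effect per visit, the bias was about 1 point.

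**Step 3: second set of assumptions.** 4,000 patients per scenario; week-104 recovery set near 60%; more dropout when the last state is poor. Weighted GEE uses the true observation probabilities. Week 104:

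| Recovery process | Dropout, poor / good | True | Independence | Exchangeable | Weighted |
|---|---|---|---|---|---|
| Exchangeable | 12% / 3% | 0.596 | 0.641 (+4.5) | 0.590 (−0.6) | 0.588 (−0.8) |
| Exchangeable | 8% / 3% | 0.602 | 0.631 (+2.9) | 0.608 (+0.6) | 0.604 (+0.2) |
| Autoregressive | 12% / 3% | 0.608 | 0.662 (+5.4) | 0.596 (−1.2) | 0.609 (+0.1) |
| Autoregressive | 8% / 3% | 0.591 | 0.628 (+3.7) | 0.595 (+0.4) | 0.597 (+0.6) |
| Irreversible | 12% / 3% | 0.597 | 0.682 (+8.5) | 0.595 (−0.2) | 0.590 (−0.7) |
| Irreversible | 8% / 3% | 0.595 | 0.648 (+5.3) | 0.603 (+0.8) | 0.598 (+0.3) |

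With constant dropout, independence gave −0.2 to +1.0 points, which is simulation noise.

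**Step 4: continuous outcome, SD 20.** Under the same two dropout patterns the bias was +1.5 to +2.9 with independence. With exchangeable correlation it was −0.1 to −0.2 in three scenarios and −1.0 in the fourth (autoregressive truth, 12% / 3%). Weighted estimates lay within about 0.3 of the truth.

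**Step 5: scale.** With all 72 patients observed, the standard error of a 50% proportion is √(0.5 × 0.5 / 72) = 0.059. A bias of 3 to 11 points is about 0.5 to 1.9 standard errors (2.9/5.9 and 11/5.9).

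**The case against.** A reader might infer that GEE is valid only under missing completely at random and that the planned curves will be biased. The documents do not support that. GEE also remains valid when missingness depends only on modelled covariates, and time, aetiology and age are planned. With exchangeable correlation the recovery bias was about a point. This limits the claim to possible bias. It does not rescue the sentence: predictors enter one at a time, so most models condition on little, and the working correlation that would help is not stated.

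A reader might also infer that early programme end and dispersal after discharge lose data. They do not by themselves. A measurement is planned at discharge, later visits are timed from admission whatever the length of stay, and a research assistant visits patients wherever they live. Among these routes, re-consent is the clear outcome-linked one, and no refusal rate is given.

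The simulations have limits. Their rates are invented. The 62% against 51% case, and all of step 3, have non-recovered patients leaving more often, which is the opposite of what re-consent would do. Visit was a factor, whereas the plan enters time in weeks. Bias in predictor coefficients was not examined. The size is therefore illustrative.

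The quality-of-life models will lose records with a missing time-dependent covariate, but mixed models would lose them too, so this does not count against GEE in particular.

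Weights or a working correlation may be specified in a fuller document. That would add to the sentence, not correct it.

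**Conclusion.** The point holds in limited form. The stated reason for not imputing is wrong as a general rule, and it is wrong under the very assumption the plan makes. Where dropout depends on earlier observed recovery, week-104 recovery was off by about 1 point or less with exchangeable working correlation and by about 3 to 11 points with independence, in either direction. These figures rest on assumed dropout and recovery rates. The article fixes neither the size nor the sign. That no weights will be used is an inference from silence, and the extension to quality of life, participation and caregiver outcomes rests on their sharing the method.

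This is a should-fix. The study is a single cohort with no treatment comparison, and proportions making each transition are also reported descriptively. The error matters for the recovery course and for benchmarking, and it can be corrected before analysis.

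**What to change.** Delete the justification and replace it with one of these:

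- multiple imputation followed by GEE; or
- GEE weighted by the inverse probability of observation, with stabilised weights from a small model (last observed CRS-R state and a few baseline covariates). With 72 patients, a larger weight model may be unstable.

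State the working correlation. Handle death separately from missing data; do not weight or impute past it. Keep ordinary GEE as a sensitivity analysis.

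For the continuous outcomes, linear mixed models are an acceptable alternative. For recovery, a logistic mixed model would change the estimand from population-average to subject-specific effects, so it is not a like-for-like replacement.

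Cost: revised wording, a little more programming and somewhat wider intervals. No new data are needed.

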The **D**isorders **o**f **C**onsciousness **T**reatment and **O**utcomes **R**egistry (DOCTOR) is a prospective follow-up study on outcomes for all patients ≥16 years in UWS and MCS and their families who entered the EIN programme in one designated expert rehabilitation centre in the Netherlands. It is a 14-week subacute intensive neurorehabilitation programme for patients discharged from the intensive care unit or hospital ward, to improve (recovery of) consciousness, prevent complications and empower caregivers.

In DOCTOR outcomes of patients with PDOC are recorded systematically with a follow-up of 24 months after admission to EIN. Main outcome measures are (predictors) of recovery of LOC, mortality, incidence and type of complications, outcomes in terms of level of disability, including the level of motor, cognitive, behavioural and emotional functioning, pain, cognition, participation and quality of life. Further, caregiver burden and self-efficacy will be assessed as well as cost-effectiveness.

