### Mortality

We will register the following causes of death: [28].
Death from (co) morbidity despite treatmentDeath from comorbidity after a non-treatment decision (non-resuscitation or withholding treatment for medical complications)Death after withdrawal of artificial nutrition and hydration.

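### The recovery GEE has no rule for death, so modelled recovery can rise as unrecovered patients die

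*Protocol article*

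**What the plan says.** All references are to the protocol article. Under Statistical analysis, the course of recovery of consciousness "will be analysed using Generalized Estimating Equations (GEE) analysis for logistic outcomes on an intention-to-treat basis". The outcome is set as "Recovery (yes/no) at each time point will be included as the dependent variable in the GEE model". Two such models are planned: "Separate models will be generated for transitions from UWS to MCS and from MCS to the fully conscious state based on the CRS-R". The CRS-R is described under Measurement instruments as a bedside observation of responses.

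The missing-data rule is "Assuming that data are missing at random, data imputation is unnecessary in GEE analysis", and the reason added is that "all observations are taken into account in contrast to complete case analyses".

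Death is dealt with elsewhere. The Background section says "Main outcome measures are (predictors) of recovery of LOC, mortality, incidence and type of complications". The Mortality section registers three categories of death: despite treatment, after a non-treatment decision, and "Death after withdrawal of artificial nutrition and hydration".

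No section connects the two. Death is not coded as non-recovery, is not named as a competing event, and is not part of a composite. The recovery result is not declared to apply only to patients while alive.

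**The concern.** A patient who has died cannot be assessed with the CRS-R. A model built on observed records, without imputation, therefore receives nothing from that patient after death. The missing-at-random sentence does not cover this, because status after death is not an unobserved value; it does not exist. Even for ordinary dropout the sentence is weak support: unweighted GEE generally needs data missing completely at random given the covariates, not merely missing at random.

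Two of the three registered categories of death follow a decision to withhold or withdraw treatment. It is plausible that such decisions are taken more often when consciousness has not returned. If so, each death removes mainly non-recoveries from the later visits, and the modelled proportion recovered goes up without any patient recovering. The estimated effect of any predictor that also predicts death can be distorted in the same way.

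The Discussion section offers recovery patterns and predictors as the study's product, for benchmarking the programme and improving outcome prediction. A period with more deaths among unrecovered patients could then look like a period with better recovery.

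**Working it through.** **Inputs.** N = 72, from the Data collection section ("In 4 years we aim to include 72 patients"). The article gives no calculation behind 72 and no mortality figure, so there is no planned figure to reproduce. The number recovered, the number of deaths and their split by recovery status are assumptions, shown as ranges.

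**Step 1: arithmetic.** Let R be the number ever recovered, D the deaths and D_R the deaths among the recovered, with no further recoveries.

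- Ever recovered among all enrolled = R / N
- Recovered among survivors = (R − D_R) / (N − D)

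With R = 36, R / N = 36/72 = 50.0%. Recovered among survivors is then:

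| Deaths | All among unrecovered | 80% among unrecovered | In proportion to status |
|---|---|---|---|
| 7 (9.7%) | 36/65 = 55.4% | 34.6/65 = 53.2% | 32.5/65 = 50.0% |
| 14 (19.4%) | 36/58 = 62.1% | 33.2/58 = 57.2% | 29/58 = 50.0% |
| 22 (30.6%) | 36/50 = 72.0% | 31.6/50 = 63.2% | 25/50 = 50.0% |

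With R = 24 (24/72 = 33.3%), the first column becomes 36.9%, 41.4% and 48.0%, and the second 34.8%, 36.6% and 39.2%.

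The survivor proportion rises only if the unrecovered make up a larger share of the deaths than of the cohort. With R = 12, they are 60/72 = 83% of the cohort. If they account for only 80% of deaths, the proportion falls slightly, from 16.7% to 16.3%, 15.9% and 15.2%.

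**Step 2: does a fitted GEE behave this way?** Logistic GEEs with a term for each visit (weeks 5, 10, 14, 28, 40, 52, 104) were fitted to 8,000 simulated patients per scenario, with no records after death. The assumed recovery hazard was 0.02 per week until week 28 and zero after, so any rise after week 28 is artificial.

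| Weekly death hazard, unrecovered / recovered | Alive at week 104 | Ever recovered, all enrolled, weeks 28 to 104 | Independence GEE, week 28 → 104 | Exchangeable GEE, week 28 → 104 |
|---|---|---|---|---|
| 0.003 / 0.003 | 73.1% | 40.6% | 42.3% → 41.9% | 42.3% → 42.1% |
| 0.003 / 0.0005 | 81.1% | 41.6% | 44.0% → 48.8% | 43.4% → 44.8% |
| 0.008 / 0.0005 | 61.7% | 39.2% | 46.0% → 60.4% | 43.8% → 47.9% |

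The independence fit equals the raw proportion among survivors. The exchangeable fit lies between that and the all-enrolled proportion. It still rises when deaths concentrate among the unrecovered, but by less. With equal hazards neither fit rises after week 28.

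**The case against.** The article never says that patients who die are dropped. It is a condensed text, and intention-to-treat could be meant to keep every included patient, with the dead scored as not recovered. That is fair as to intention, so the exclusion is a default consequence and not a stated rule. But the label assigns no value after death, and the only missing-data rule given leads the other way.

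A reader might infer more than the documents support:

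- **That the model estimates recovery among survivors.** This is exact only under an independence working correlation, and the article names none.
- **That 72% against 50% is the expected error.** Those figures require every death to be among the unrecovered, and 36/72 is illustrative. It is not the denominator of either planned transition model.
- **That recovery climbs even if nobody ever recovers.** With no recoveries it stays at 0%. The claim concerns a rise without further recoveries.
- **That age or aetiology effects are shown to be distorted.** The Background section lists younger age and traumatic aetiology as prognostic for recovery. No section names predictors of death, so only the general mechanism stands.
- **That 50% is the one true answer.** Recovery while alive is a legitimate target if it is declared and shown with mortality.

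The plan also has partial safeguards: separate descriptive transition proportions, and mortality as an outcome in its own right. The denominator of those proportions is not stated, and neither safeguard changes what the GEE estimates.

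**Conclusion.** The concern holds as a fault in the analysis as written. The outcome, the source of status and the missing-data rule are all fixed, and followed literally they leave a patient without records after death. The justification given does not cover death, and no while-alive estimand is declared.

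The direction rests on deaths being over-represented among unrecovered patients. The registered causes make this plausible but do not establish it. The size runs from no artificial rise, when death is unrelated to recovery, to the upper bounds in the first column of the arithmetic. It also depends on the unstated working correlation. No distortion of a particular predictor can be quantified from the document.

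**What to change.** In the Statistical analysis section, define the outcome at each planned visit, for all included patients in the respective model, as alive and recovered (at least MCS, or conscious) versus not, with death counted as not recovered. Report the cumulative incidence of each transition with death as a competing event. The Mortality section mentions causes of death but not dates, so record the date of death if it is not already collected. If recovery while alive is also reported, label it as such and show it beside mortality.

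A multi-state model (UWS, MCS, conscious, dead) is optional. With 72 patients and no planned visit between weeks 52 and 104, it may be too sparse to carry covariates.

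The change needs no extra patients or visits. Its price is that reported recovery percentages become lower, and that patients who recover and later die count as not recovered at later visits. The cumulative incidence keeps those recoveries visible.

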**Inclusion criteria**	
Age16 years or older	
PDOC (UWS or MCS) lasting > 4 weeks and < 6 months at admission to EIN	
First-time newly acquired non-progressive brain injury of any aetiology	
Weaned from ventilator	
Medically stable, as judged by the treating rehabilitation physician	

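### The recovery models described as transition models take status at each visit as outcome, so they estimate the probability of being in a state; the outcome and who enters each model should be worded to match

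*Protocol article*

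**What the plan says.** All of the following is in the protocol article.

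- **Outcome.** Statistical analysis: "Recovery (yes/no) at each time point will be included as the dependent variable in the GEE model".
- **Purpose of the models.** The next sentence of that section: "Separate models will be generated for transitions from UWS to MCS and from MCS to the fully conscious state based on the CRS-R".
- **Predictors.** The listed independent variables are "measurement time (weeks), traumatic vs. non-traumatic aetiology, age at injury, and complications (yes/no or number"). Neither baseline level of consciousness nor state at the previous visit is among them. The Background names level of consciousness at admission as a prognostic factor.
- **Baseline state.** Table 1 admits patients with "PDOC (UWS or MCS) lasting > 4 weeks and < 6 months at admission to EIN", so both states are present at entry. In the analysis, baseline state appears only as a grouping: "Subgroup analyses will be performed for patients presenting in UWS versus MCS at baseline".
- **Descriptive transitions.** These are planned separately: "The proportions of patients transitioning from UWS to MCS and emergence from MCS to the conscious state will be calculated during and after EIN".
- **Schedule.** Data collection sets visits at the start and at weeks 5, 10 and 14, with consciousness assessed weekly during EIN. After discharge, "follow-up measurements are planned at 28, 40, 52, and 104 weeks post-inclusion".
- **Missing data.** "Assuming that data are missing at random, data imputation is unnecessary in GEE analysis". That sentence does not mention death, which is itself an outcome of the study.

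**The concern.** A transition is a move from one state to another among patients still at risk of it. A marginal GEE on status at every visit has no at-risk set. It describes what proportion of observed patients are in the recovered state at each time. Measurement time is a listed predictor, and the article promises insight into recovery patterns. A reader told that these are transition models could therefore take a rising time effect to mean that recovery becomes more likely as time passes, when the weekly chance may be flat or falling.

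The second issue is who enters the model that starts from MCS. Patients admitted in UWS can also become conscious. If the wording is applied literally, some or all of their emergences could fall outside the model, in a study that aims for 72 patients.

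**Working it through.** The article gives no transition rates, no UWS/MCS split and no sample-size derivation, so there is no figure of its own to reproduce. Every rate below is an assumption and shows direction and rough size only.

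**1. Status versus transition.** Without relapse or death, a patient recovered by week 5 contributes 7 recovered rows (weeks 5, 10, 14, 28, 40, 52, 104). One first seen recovered at week 52 contributes 2. The model therefore follows the accumulated proportion in the state. A weekly three-state simulation (20,000 patients, half entering in UWS, scheduled visits, independence working correlation) gave:

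| Assumed weekly rate | MCS-to-conscious probability per week, given MCS at previous visit | Status GEE, odds ratio per week |
|---|---|---|
| 3%, constant, no death or relapse | flat, about 0.029–0.031 | 1.05 |
| 6% at first, then falling; death 0.5%, relapse 0.3% | falls from 0.056 to 0.006 | 1.03 |

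In the first row the proportion conscious rises from 0 to 0.89 by week 104 although the rate never changes. In the second, the two quantities move in opposite directions.

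**2. If only baseline-MCS patients enter.** Assume 2% per week for each transition, at most one step per week, and no death.

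- Conscious by week 104 from MCS: 1 − 0.98^104 = 1 − 0.122 = 0.878.
- Conscious by week 104 from UWS: 1 − 0.98^104 − 104 × 0.02 × 0.98^103 = 1 − 0.122 − 0.260 = 0.618.
- Share of emergences from UWS starters, for entry share s: 0.618s / [0.618s + 0.878(1 − s)].

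| Variant | From UWS | From MCS | s = 30% | s = 50% | s = 70% |
|---|---|---|---|---|---|
| 2% per week, no death | 0.618 | 0.878 | 23% | 41% | 62% |
| UWS-to-MCS rate 6% in an assumed 40% traumatic | 0.698 | 0.878 | 25% | 44% | 65% |
| 2% per week, death 0.5% per week | 0.471 | 0.743 | 21% | 39% | 60% |

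The range is about 21–65%. At s = 50% in the first row, 72 × 0.5 × 0.618 = 22 of 72 × 0.5 × (0.618 + 0.878) = 54 emergences come from UWS starters.

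**3. If a prior observed MCS assessment is required.** Use weekly assessment to week 14, then weeks 28, 40, 52 and 104. Over a gap of g weeks, the chance of going from UWS to conscious is 1 − 0.98^g − g × 0.02 × 0.98^(g−1). The chance of still being in UWS at the start of the gap, week t, is 0.98^t.

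| Gap (weeks) | Still in UWS | UWS to conscious in the gap | Product |
|---|---|---|---|
| 14–28 | 0.754 | 0.031 | 0.023 |
| 28–40 | 0.568 | 0.023 | 0.013 |
| 40–52 | 0.446 | 0.023 | 0.010 |
| 52–104 | 0.350 | 0.279 | 0.098 |

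The sum is 0.144, and 0.144 / 0.618 = 23% of UWS starters who become conscious are never seen in MCS first. With the faster rate in traumatic patients this is 16%, and adding death to that variant leaves it at 16%. Simulation of the same setting gave 16–24%; the wider range is quoted. Weekly assessment helps little because most of the loss comes from the 52-week gap.

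**4. If all patients enter the model for consciousness.** No emergence is lost. The model is then plainly one of the probability of being conscious at each visit.

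**The case against.** The strongest reply is that the GEE is introduced as an analysis of the course of recovery over time, and a marginal model of status suits that aim. Transitions have their own descriptive proportions. The sentence on separate models can be read as naming two thresholds for recovery. This largely stands: the model type is acceptable, and the fault is the label and what a reader would draw from it.

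Three stronger readings are tempting but not supported:

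- **That the analysis will lose a large share of events.** The article states no restrictive entry rule. Its intention-to-treat wording and its use of all observations are compatible with every patient entering. An article may leave entry sets to the full protocol or analysis plan, so their absence is not the finding.
- **That repeated recovered rows count one event several times.** Repeated binary outcomes are normal in GEE, which allows for within-patient correlation.
- **That the predictor odds ratios are biased.** No material bias was found in the assumed scenario that was examined.

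It is also true that, within one baseline state and with no relapse or death, status at a visit equals the cumulative proportion who have made the transition. The article states no such restriction, and it records mortality as an outcome.

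**Conclusion.** The point holds as a mismatch between the stated outcome and the stated purpose. The models estimate the probability of being at or above a level of consciousness among patients observed at each visit, and their time effect must not be reported as a transition rate. This follows from two adjacent sentences and needs no assumed figure.

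The risk to UWS starters is conditional on the entry rule. It covers about 21–65% of all emergences under a baseline-MCS rule, about 16–24% of UWS starters' emergences under a prior-MCS rule, and none if everyone enters. These sizes rest on assumed rates near 2% per week and entry UWS shares of 30–70%. A correction is worthwhile because level of consciousness is the first outcome listed in the abstract, the cohort is small, and a prognostic factor that the Background itself names is missing from the predictor list.

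**What to change.** Replace the sentence on separate models with two models of state probability:

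1. Patients in UWS at baseline; outcome MCS or better at each visit.
2. All patients; outcome conscious at each visit, with baseline level of consciousness (UWS or MCS) as a covariate.

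Describe both as models of the course of recovery, not of transitions. Restricting or adjusting for baseline state does not change what they estimate, so the label matters.

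Only if transition rates are wanted, add a secondary model on at-risk intervals (state at one assessment to state at the next), with a complementary log-log link and log interval length as offset. State how a move from UWS to conscious within one interval is assigned.

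The cost is one extra covariate with 72 patients, a change of wording and modest programming. No new data are needed, and the second model keeps every observed emergence.
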